#### Control group (‘Advice Only’ group)

Following baseline measurements, participants randomized to the ‘Advice Only’ control group will receive an email at the same time as the FA group informing them that they will receive their test result by the end of the academic year, resembling a ‘wait-list control’ group for the gene test feedback condition. The weight control advice leaflet will be attached to the email, matching the format of the intervention group. Ethical concerns about withholding weight control advice from individuals at increased risk of weight gain, and the likelihood of contamination between groups, led to the decision to send the leaflet to all participants and therefore not to have a ‘no treatment’ control group that receives neither leaflet nor genetic feedback. The gene test result will be sent out in identical format to the intervention group at the end of the academic year after collection of follow-up anthropometric data is complete.

### Randomization

All consenting participants will be randomized to ‘FA’ (intervention) or ‘AO’ (control) after baseline data collection is complete and records have been anonymized using serial numbers. For group allocation, we will use the randomization function in the Statistical Package for Social Sciences (SPSS 19 for Windows®; SPSS Inc., Chicago, IL, USA), which randomly assigns a set percentage of cases to a specified number of groups. Each group will consist of 400 participants, and based on population frequencies of *FTO* we expect 252 to have at least one higher-risk (A) allele and 148 to have the lower-risk (TT) genotype. Randomization will take place after data collection of each wave is complete, but before the DNA analyses are conducted. Experimenter bias is unlikely, as records are anonymous and not easily identifiable. Although neither researchers nor participants will be blind to group allocation, follow-up weights will be measured objectively and print-out records kept, which excludes inadvertent manipulation of records. Questionnaire data will be collected online, which minimizes the risk of missing data or inadvertent manipulation.

### Minimizing other sources of bias

Participants who will select themselves into the study are likely to be more positive towards genetic testing than the average student population. However, if genetic testing were offered through a healthcare provider or over the internet, the same situation would hold; that is, only interested individuals would choose to take part, and this situation therefore should not unduly influence the generalizability of the results.

### Recruitment and consent

Ethical approval was granted by the University College London Research Ethics Committee for non-NHS research in September 2010. Participants will be recruited at the beginning of two consecutive academic years. Potential participants will be recruited through emails sent to all first year students (approximately 22,000) enrolled at University College London (UCL) inviting them to take part in a study where they will receive information on their personal genetic risk for weight gain susceptibility. A ‘collection station’ will be set up at UCL in the first two weeks of term where participants can receive detailed information about the study, check eligibility, enroll, and give saliva for DNA analysis. To ensure that participants are aware of the details of the study, information contained in the information sheet will be reiterated by a researcher. Participants will be told that the DNA analysis is only for one gene (*FTO*) which is related to a small increase in weight gain susceptibility and that students will be randomly allocated to receive their results either during term 2 (intervention group) or at the end of the academic year (control group). Participants will be informed that their samples will be destroyed on completion of the study and not stored for further analyses. Written consent will be obtained before participants give saliva for DNA analysis. The right to withdraw from the study without giving reason will be respected at all times, and saliva samples will be destroyed immediately after participant withdrawal.

### Participants

Participants will be a volunteer sample (n = 800) of first year university students.

#### Inclusion and exclusion criteria

We will include all interested first-year students between 18 and 25 years who are able to give informed consent. We chose this age range because the association between *FTO* and BMI has been found to peak in early adulthood, with less effect thereafter [25]. As *FTO* has been found to have effects in all major ethnic groups, we will not exclude participants based on ethnicity. We anticipate that a small number of individuals suffering from eating disorders may express interest in taking part, because eating disorders are relatively common in this age group [26]. However, participants have the option of declining to see weight and body composition results. If they opt to receive their body composition assessment, they will get brief, personal feedback with it. We will be careful to avoid discriminating against anyone based on their weight (high or low) because this may impair help seeking. Instead, we will offer brief, general advice on available resources to all participants, so that those who wish to find help can do so. If a participant is distressed by the result, the principal investigator, who is a clinical psychologist, will be available for intervention. Results from earlier qualitative work indicate that gene test feedback may be helpful even for individuals with a history of eating disorders, and that provision of information should be sufficient to eliminate the risk of exaggerating tendencies for disordered eating ([name] and JW, unpublished).

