#### Baseline questionnaire

The baseline questionnaire will be sent by email after anthropometric data and saliva have been collected. It will include demographic and health-related measures (age, gender, course of study, year of study, family history of overweight), and standardized questionnaires assessing the following: *Diet quality* will be determined using the using the DINE, which is a self-report food frequency questionnaire, commonly used in clinical practice, assessing dietary fat, fiber and fruit and vegetable content [29]. *Eating behavior* will be assessed with the Dutch Eating Behavior Questionnaire (DEBQ), which determines tendencies for emotional eating, restraint eating and external eating [30]. *Physical activity* will be assessed with the Recent Physical Activity Questionnaire (RPAQ), which assesses time and frequency for a range of physical activities for commute and leisure [31]. *Stress* will be determined using the Perceived Stress Scale-4 (PSS-4, [32]. The PSS-4 is a short version of the 20-item perceived stress scale, with good psychometric properties [33]. Four items will assess *worry about weight gain*[34] and *diet self-efficacy*[35]. All questionnaires have sound psychometric properties and are commonly used in clinical practice.

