### Statistical analyses

Differences between completers and non-completers of follow-up will be assessed with chi-square tests for categorical variables and independent-samples *t*-tests for continuous variables. Participants who had been controlling their weight for more than one month will be excluded from analysis, because the intervention will not be applicable. Correct recall of the test result will be assessed with a chi-square test. Associations between genotype status and correct recall will be assessed with a one-way ANCOVA, including age, gender and body mass index (BMI) as covariates, as recall may affect subsequent reactions.

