#### Secondary

Results from all secondary analyses will be considered as exploratory. One-way ANOVAs, followed by one-way ANCOVAs will be used to examine immediate psychological reactions to genetic test feedback in the sample overall once the AO group participants have received their genetic test results. Repeated-measures ANOVAs will be used to determine change in anthropometric measures within groups over time in the sample overall. Anthropometric differences between groups will be determined using one-way ANCOVA. Age, gender and baseline BMI will be included as covariates. Changes in diet quality, eating behavior and physical activity in the sample overall will be examined with repeated-measures ANOVAs. Changes between groups will be examined using one-way ANCOVAs, including age, gender and baseline BMI as covariates. Group differences in actual behavior change (as measured by adherence to the individual tips) will be assessed with a one-way ANCOVA. In addition, we will build an additive score of the total number of tips adhered to at least ‘occasionally’ and compare this in intervention and control group with a one-way ANCOVA. Age, gender and baseline BMI will be included as covariates. Bonferroni corrections will be used for multiple comparisons in all analyses. Within the ‘Feedback and Advice’ group, *FTO* status will be dichotomized into high/average risk, with those having at least one risk allele being classified as ‘higher-risk’. Ordinal regression analyses will be used to examine effects of risk status on motivation to control weight, as well as interactions between risk status and baseline BMI. Age and gender will also be included as predictor variables in the model. Finally, we will assess predictors of motivation to control weight with a multinomial regression analysis. We will include all potential predictors, including age, gender, *FTO* status, as well as stress, eating behavior, baseline BMI, and weight satisfaction.

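### Entry is open to all ethnic groups but no stated genotype model names ethnicity, so the exploratory higher- v average-risk comparisons are open to confounding by ancestry

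*Protocol article*

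**What the plan says.** All references are to the protocol article.

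- **Inclusion and exclusion criteria.** On entry, the article says "we will not exclude participants based on ethnicity". The reason given is that FTO is reported to act in every major ethnic group.
- **Randomization.** "Each group will consist of 400 participants", and within each group "we expect 252 to have at least one higher-risk (A) allele and 148 to have the lower-risk (TT) genotype". The split is described as "based on population frequencies of" FTO, with no allele frequency, reference population or citation.
- **Baseline questionnaire.** The items include "demographic and health-related measures (age, gender, course of study, year of study, family history of overweight". Ethnicity is not in the list.
- **Statistical analyses (opening paragraph).** Correct recall by genotype is analysed "including age, gender and body mass index (BMI) as covariates".
- **Statistical analyses, Secondary.** Within FA, carriers of at least one A allele are compared with TT on motivation by ordinal regression, with an interaction between risk status and baseline BMI. For this model, "Age and gender will also be included as predictor variables in the model". A multinomial model of motivation has FTO status among a wider, open-ended set of predictors. Ethnicity is not named in either.
- **Secondary research objectives.** The hypotheses include higher negative affect but not higher fatalism after a higher-risk result than after an average-risk one, and more motivation among overweight participants with a higher-risk result. All secondary objectives are declared exploratory because power is limited.

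**The concern.** The reason given for open entry concerns the effect of the gene, which is said to be present in all major ethnic groups. It does not address whether carrier rates, or the psychological and motivational outcomes, are alike across those groups.

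Randomisation balances ancestry between FA and AO, apart from chance. It does not balance ancestry between carriers and TT participants, because genotype is observed and not assigned. If one ethnic group has fewer carriers and also tends to answer differently on motivation or affect, that group is over-represented among TT, and its different answers appear as an effect of the test result. Age, gender and BMI cannot be relied on to remove this.

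At stake is the reading of the higher- v average-risk comparisons. The bias can create a difference or hide one, so a finding of no greater fatalism is as exposed as a finding of greater motivation.

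**Working it through.** **1. The plan's split.** 252 + 148 = 400; 252/400 = 0.63 carriers; 148/400 = 0.37 TT. Under Hardy-Weinberg proportions the TT share is (1 − p)², so p = 1 − √0.37 = 0.392. The split is coherent and fits a single A-allele frequency near 0.39. It cannot be derived from the document, which gives no p.

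**2. Covariates stated for genotype analyses.**
- Recall by genotype: age, gender, BMI.
- Risk status on motivation within FA: age, gender, and baseline BMI through its interaction with risk status.
- Multinomial model: age, gender, FTO status, stress, eating behaviour, baseline BMI, weight satisfaction; open-ended.
- Immediate psychological reactions: ANOVA, then ANCOVA; ethnicity not named.

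**3. Size of a possible bias.** Every input except the 63% is assumed. Let a share s of participants belong to a group with A-allele frequency q, the rest having 63% carriers, and let the two groups' outcomes differ by δ SD with no true genotype effect.
- Carrier share in the lower-frequency group: c = 1 − (1 − q)². For q = 0.15, c = 0.2775; for q = 0.20, c = 0.36.
- Overall carrier share: C = (1 − s) × 0.63 + s × c.
- Share of that group among carriers: s × c / C. Among TT: s × (1 − c) / (1 − C).
- Spurious difference = δ × (share among TT − share among carriers).

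| s | q | Carriers/TT per 400 | Share of carriers | Share of TT | Gap (points) | Bias, δ = 0.2 | Bias, δ = 0.5 |
|---|---|---|---|---|---|---|---|
| 20% | 0.20 | 230/170 | 12.5% | 30.2% | 17.7 | 0.04 SD | 0.09 SD |
| 20% | 0.15 | 224/176 | 9.9% | 32.8% | 22.9 | 0.05 SD | 0.11 SD |
| 40% | 0.20 | 209/191 | 27.6% | 53.6% | 26.0 | 0.05 SD | 0.13 SD |
| 40% | 0.15 | 196/204 | 22.7% | 56.6% | 33.9 | 0.07 SD | 0.17 SD |

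The range runs from 0.177 × 0.2 = 0.035 SD to 0.339 × 0.5 = about 0.17 SD. If q equals the frequency in the rest of the intake, the gap is zero; if δ = 0, the product is zero.

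**4. Effect on false positives.** Take 200 FA participants with data, which is half of 400, in line with the attrition expected under Minimizing drop out. With s = 30%, q = 0.15 and δ = 0.3:
- C = 0.7 × 0.63 + 0.3 × 0.2775 = 0.524, or about 105 carriers and 95 TT.
- The group is 15.9% of carriers and 45.6% of TT, so the bias is 0.297 × 0.3 = 0.089 SD.
- The standard error is √(1/105 + 1/95) = 0.142, and 0.089/0.142 = 0.63.
- The two-sided rejection rate is Φ(0.63 − 1.96) + Φ(−0.63 − 1.96) = 9.6% instead of 5%.

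Over the assumed ranges in step 3, the rate runs from 5.7% to 22%. The SD scale stands in for the ordinal outcome, and no covariate adjustment is modelled.

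**5. What rests on 252/148.** The sample-size section concerns FA v AO and does not use the split. A different split would also change precision little: for 0.25 SD and 200 people, power is 40% at 126/74 and 42% at 100/100.

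**The case against.** The strongest reply is that the point concerns only exploratory analyses and that its size is built on assumptions. Nothing in the document says that allele frequency, motivation or affect differs by ethnic group, and without both kinds of difference there is no bias. Most of the illustrated range is small. All of that stands. It limits the weight of the point without answering it, because the exploratory label is justified by limited power and does not remove a bias.

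Some stronger readings are tempting, and the documents do not support them.
- *A reader might infer that ethnicity is not collected.* The baseline list is not complete: the multinomial model uses weight satisfaction, which that list does not mention. A condensed article may leave out other items too. The stated covariate sets are the firmer evidence.
- *A reader might infer that the problem cannot be repaired later.* Self-reported ethnicity can be asked for as long as participants can be contacted, and questionnaires already go out by email. What would be lost is recovery from DNA, since samples are to be destroyed on completion.
- *A reader might infer that 252/148 is wrong.* It is coherent, and showing it wrong needs group frequencies and an intake mix that are not given. Only its source is unstated.
- *A reader might infer that every genotype model adjusts only for age, gender and BMI.* The multinomial model has a wider, open-ended set.
- *A reader might count the hypothesis about valuing an explanation for one's weight among those exposed.* As worded, it compares overweight with normal-weight participants, so it is not a carrier v TT contrast.

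**Conclusion.** The point holds for the genotype comparisons. Entry is open to all ethnic groups, genotype is not randomised, and no stated model with genotype or risk status as exposure names ethnicity. The higher- v average-risk comparisons of negative affect, fatalism, recall, and motivation with its BMI interaction are therefore open to confounding by ancestry.

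The possible size is about 0.04-0.17 SD under the assumed inputs. It depends on carrier rate and outcome both varying by ethnic group, which the documents neither establish nor rule out. The randomised FA v AO comparisons, including the primary one, are untouched, as are the sample size and power statements. This is a worthwhile, inexpensive correction to exploratory analyses and no threat to the trial's main conclusion.

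**What to change.** 1. Confirm that the baseline questionnaire records self-reported ethnicity. If it does not, add one item and send it by email to participants already enrolled. Recruitment is still in progress, so this is feasible.
2. Name ethnicity as a covariate in every analysis where FTO genotype or risk status is the exposure: recall, psychological reactions, the ordinal regressions within FA, and the multinomial model.
3. Optionally, state the allele frequency and reference population behind 252/148. This is clarification only.

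The cost is one questionnaire item, with an ethics notification if it is new, and a few model degrees of freedom. No extra participants or procedures are needed.

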### Proposed study duration

The study will run over three university terms (eight months).

## Measures

### Baseline

#### Body composition

Participants will be asked to remove shoes, socks and heavy items, but stay otherwise fully clothed. Height will be measured, rounded up to the nearest centimeter, using the Leicester Height Measure, a standardized instrument for determining height. Weight and body fat will be assessed using the TANITA TBF-300 MA Body Composition Analyzer (Tanita, Tokyo, Japan). This uses electrical impedance to assess body fat which compares well to other measures of body composition such as whole body magnetic resonance imaging and dual X-ray absorptiometry [27]. Participants can opt to receive a printout of the results together with an explanation by the research team or not.

#### DNA Collection and genotyping

Participants will be asked to give a saliva sample for DNA collection by placing some sugar onto their tongue to stimulate saliva flow and then ‘drooling’ into a plastic tube to generate 1.5-2 ml of saliva. Samples will be coded with a unique identifier number so that they are anonymous but can be linked back to questionnaire data. DNA will be isolated and extracted from saliva. Genotyping of *FTO rs9939609* will be performed using TaqMan; details of extraction and analysis methods have been published elsewhere [28]. Samples will be analyzed at the Institute of Metabolic Sciences, Cambridge, which is a certified research laboratory.

#### Baseline questionnaire

The baseline questionnaire will be sent by email after anthropometric data and saliva have been collected. It will include demographic and health-related measures (age, gender, course of study, year of study, family history of overweight), and standardized questionnaires assessing the following: *Diet quality* will be determined using the using the DINE, which is a self-report food frequency questionnaire, commonly used in clinical practice, assessing dietary fat, fiber and fruit and vegetable content [29]. *Eating behavior* will be assessed with the Dutch Eating Behavior Questionnaire (DEBQ), which determines tendencies for emotional eating, restraint eating and external eating [30]. *Physical activity* will be assessed with the Recent Physical Activity Questionnaire (RPAQ), which assesses time and frequency for a range of physical activities for commute and leisure [31]. *Stress* will be determined using the Perceived Stress Scale-4 (PSS-4, [32]. The PSS-4 is a short version of the 20-item perceived stress scale, with good psychometric properties [33]. Four items will assess *worry about weight gain*[34] and *diet self-efficacy*[35]. All questionnaires have sound psychometric properties and are commonly used in clinical practice.

### Follow-up

#### Primary outcome

The primary outcome is motivation to engage with weight gain prevention. It will be assessed using a validated measure of readiness for behavior change [36,37] adapted to relate to prevention of weight gain. Individuals will be asked: *‘*Please mark with an ‘X’ the statement out of the next four that best describes you’: ‘I am not trying to control my weight, and I have no intention of doing so in the next month’; ‘I am not trying to control my weight, but I am thinking of doing something in the next month’; ‘I started to try to control my weight within the last month’; or ‘I have been trying to control my weight for more than a month’. Responses will be used to classify individuals into one of the five stages of behavior change outlined by Prochaska and DiClemente [38]. Participants will also be asked to rate their agreement with one statement each relating to motivation to prevent weight gain, perceived ease of weight control, and the priority they are giving to weight control (ranging from ‘never’ to ‘always’*)*. The primary outcome will be measured one month after the intervention group receives their genetic test result. We chose the respective time frame, because we saw it as crucial that participants would have had sufficient time to think about their result, to ask any questions, and to implement eventual behavior change. We will exclude participants who controlled their weight for more than one month, because the intervention will not be applicable to them.

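### As written, the primary analysis excludes participants by an answer recorded only after randomisation, which is itself one level of the primary outcome

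*Protocol article*

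**What the plan says.** The exclusion is stated twice in the protocol article, each time with its reason. Under Primary outcome: "We will exclude participants who controlled their weight for more than one month, because the intervention will not be applicable to them". Under Statistical analyses: "Participants who had been controlling their weight for more than one month will be excluded from analysis".

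The primary outcome is a four-statement readiness item, listed under Follow-up. Its fourth statement is "I have been trying to control my weight for more than a month". On timing: "The primary outcome will be measured one month after the intervention group receives their genetic test result".

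Randomisation is placed earlier, "after baseline data collection is complete and records have been anonymized using serial numbers". The Baseline questionnaire section lists demographics, family history, diet quality, eating behaviour (DEBQ), physical activity, stress, weight-gain worry and diet self-efficacy. It lists no readiness stage and no duration of weight control. The eligibility criteria do not bar people who are already controlling their weight. The primary analysis is an ordinal logistic regression of FA versus AO, with age, gender and baseline weight status as further predictors.

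**The concern.** The reason given for the exclusion, that the intervention does not apply, concerns a person's state before the intervention. The only listed source for that state is an answer given after it. Selecting on that answer conditions the comparison on the outcome under test and removes its top level.

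This matters if option four can depend on arm, and there are two ways it can:

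- A participant who starts on reading the result but replies late, for instance after an email reminder, has by then been trying for more than a month and ticks option four.
- Feedback may lead someone already controlling their weight to persist or to lapse, which changes whether they are still in option four at follow-up.

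In either case the people left in FA and AO are no longer the groups that randomisation made alike, and the primary odds ratio is not a randomised comparison.

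**Working it through.** **Step 1: order of events, from the text.**

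1. Anthropometry and saliva, then the emailed baseline questionnaire (Baseline questionnaire). No stage or duration item is listed.
2. Randomisation, once baseline data are complete (Randomization).
3. Feedback plus leaflet (FA), or leaflet alone (AO), emailed at the same time.
4. One month later, the four-statement item (Primary outcome).
5. Exclusion of those controlling for more than a month (Primary outcome; Statistical analyses).

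The information needed at step 5 first appears at step 4, after randomisation and after feedback.

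**Step 2: which answers feedback can affect.** Someone who starts on reading the result and replies on time fits option three (started within the last month). Someone who starts at once and replies late fits option four. Someone who began before feedback is in option four if they persist and leaves it if they lapse. So option four is not fixed before randomisation, but the route for new starters is narrow.

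**Step 3: can a direction be derived?** The documents give no category shares, so this is an illustration only. Assume AO shares at one month of 40/20/10/30% for options one to four. Model: logit P(Y ≤ k) = c_k − β·FA, OR = exp(β), fitted to expected proportions, first on four levels and then with option four removed.

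| Assumed effect of feedback | FA shares (%) | Excluded, AO / FA | OR, four levels | OR after exclusion |
|---|---|---|---|---|
| 10 points leave options 1–2, all tick option 4 | 34/16/10/40 | 30% / 40% | 1.43 | 1.06 |
| Same 10 points, half tick 3 and half tick 4 | 34/16/15/35 | 30% / 35% | 1.33 | 1.34 |
| Same 10 points, all tick option 3 | 34/16/20/30 | 30% / 30% | 1.24 | 1.64 |
| 10 points of option 4 lapse to option 1 | 50/20/10/20 | 30% / 20% | 0.64 | 0.81 |
| 5 points go from option 3 to option 4 | 40/20/5/35 | 30% / 35% | 1.07 | 0.77 |

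In the first three rows the same 10 points leave options one and two. Only the box they tick differs, yet the analysed OR runs from 1.06 to 1.64. The third row is not bias in itself: exclusions are equal, and if the same people would be excluded under either arm, the higher OR simply describes non-controllers. In the other rows the excluded share differs by arm. The last row changes direction.

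**Step 4: cost of keeping everyone.** Assume 35% are long-standing controllers in both arms, with the other AO participants split 55/30/15% and OR 2.0 among non-controllers.

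- FA, first cut: odds (0.55/0.45)/2 = 0.611, so 0.611/1.611 = 37.9%.
- FA, second cut: odds (0.85/0.15)/2 = 2.833, so 2.833/3.833 = 73.9%.
- FA non-controllers are therefore 37.9/36.0/26.1%.
- Multiplying by 0.65 and adding 35% to option four gives AO 35.8/19.5/9.8/35.0% and FA 24.7/23.4/17.0/35.0%.
- The fitted four-level OR is 1.31. If all of the additional FA starters (26.1 − 15.0 = 11.1 points of the non-controllers) tick option four instead, it is 1.47.

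**The case against.** The strongest reply is that no sentence says when exclusion status is determined. The Statistical analyses wording uses a past tense that fits a pre-intervention state, and so does the reason given. The article is condensed, Figure 1 is not shown, and the listed baseline measures are evidently incomplete: the Secondary analyses use weight satisfaction as a predictor, and no listed measure covers it. A baseline item may therefore exist. This stands as a limit on certainty: the finding is that none is listed, not that none was planned. It does not remove the problem, because as printed the only source for the rule is the follow-up answer.

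Three stronger readings are tempting, and the documents do not support them.

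- **That everyone moved to act by feedback is dropped.** On-time responders who start on reading the result fit option three, and no reminder dates are given.
- **That the effect is necessarily attenuated.** Both arms get the leaflet at the same time, so AO also has starters who may answer late. Step 3 shows that the direction depends on unknown shares.
- **That the exclusion pushes the sample below what the power statement assumes.** Read literally, the 340 already allows for 60% attrition, which leaves 340 × 0.4 = 136 analysable. If 340 means completers, then 800 × 0.4 = 320 is short before anyone is excluded. Taking the stated 0.25 as Cohen's f (d = 0.5, an assumption), removing 10 to 40% of 320 leaves power of about 99% to 93%. The issue is comparability, not power.

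**Conclusion.** The concern holds in this form: the plan excludes participants from the primary analysis by a status whose only listed source is a level of the primary outcome, recorded after randomisation and open to influence by feedback. The groups analysed are then not comparable as randomised.

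Neither the size nor the direction of the bias can be derived from the documents, and the odds ratios shown rest on assumed category shares. The conclusion depends on there being no pre-randomisation measure of prior weight control. If one exists and defines the exclusion, saying so resolves the point.

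**What to change.** - Delete, under Primary outcome and Statistical analyses, any exclusion based on the follow-up answer.
- For participants still to enrol, add the same four-statement item to the online baseline questionnaire, before randomisation. Define any subset to whom the intervention applies by that answer alone, and use the answer as a covariate. This is the key part of the fix.
- Where no baseline answer exists, analyse all randomised responders on all four ordered levels, adjusting for baseline DEBQ restraint. Restraint is only a partial proxy, since it does not measure how long someone has been controlling their weight, and how much it recovers has not been calculated.
- Report the follow-up-based exclusion only as a sensitivity analysis, with counts excluded by arm.

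The cost is a wording change and one question. Recruitment spans two academic years and is in progress, so those already randomised will lack the new covariate, and the plan must say how the two sets of participants are combined. Keeping long-standing controllers also dilutes the estimate noticeably (2.0 to about 1.3–1.5 under the assumptions of step 4) and answers the question for a broader population. That estimate does compare the groups as randomised.
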